## Abstract

**Background:**

Borderline personality disorder (BPD) is a high prevalence and serious mental health disorder that has historically challenged the finite resources of health services. Despite empirical evidence supporting structured psychological therapy as the first line of treatment, there remains significant barriers in providing timely access to evidence-based treatment for this population. The primary aim of this study is to evaluate the effectiveness of providing a stepped-care structured psychological group treatment to individuals with BPD within local mental health services. The secondary aims of the study are to identify the variables that predict the need to step up or down in care and the effectiveness of treatment on psychosocial functioning.

**Methods:**

Participants seeking treatment at two community mental health services will be invited to participate. Randomised controlled trial assignment will be to either (i) group skills treatment or (ii) treatment as usual. Group treatment will be offered via a stepped-care pathway with participants initially attending a 12-week group with the option of a subsequent 16-week group. The criteria for inclusion in continuing treatment includes meeting > 4 BPD diagnostic criteria or severity on GAF (< 65) at the completion of the 12-week group. Data will be collected at baseline and at five follow-up time points over a 12-month period.

**Discussion:**

This pragmatic trial will provide valuable information regarding the effectiveness of a progressive stepped-care group treatment for individuals with BPD in the real-world setting of a community mental health service. It will further the current understanding of variables that predict treatment dose and duration.

**Trial registration:**

Australian New Zealand Clinical Trials Registry ACTRN12618000477224. Registered on 3 April 2018

## Background and rationale

Borderline personality disorder (BPD) is a high prevalence, serious mental health disorder that represents significant personal, social and economic cost [19]. People with BPD present frequently to outpatient mental health facilities and place a significant demand on hospital inpatient and emergency services [16]. Studies have reported as many as 20% of psychiatric outpatients, and over 30% of persons treated in an inpatient mental health unit have a diagnosis of BPD [2, 12, 14], with 11% of individuals also presenting with Axis I co-morbidity, e.g. mood disorder [33]. Guidelines for the treatment of BPD clearly stipulate the importance of structured psychological therapy in the community as the first line of treatment [23, 29]). Previous research has validated psychological therapies as effective in ameliorating the symptoms and the course of BPD, with several specific psychological therapies (dialectical behavioural or psychodynamic therapy) being equally efficacious and more effective than treatment as usual [6]. However, previous research is reported to be affected by issues with a heterogeneity of presentations, failure to find differences in treatment duration and frequency, and various sources of publication bias [6, 30]. The effects are small to moderate favouring BPD-tailored psychotherapeutic interventions when compared to non-specialised psychological interventions [6]. Modality of delivery has varied from individual therapy, group therapy or a combination. Limited health resources have generated an impetus for providing stand-alone group skills treatment in lieu of the standard dialectical behaviour therapy (DBT) model which combines both individual and group therapies. The findings provide overall support for the viability of stand-alone group treatment [18, 31], with a recent study conducted by Lyng et al. [20] in a community setting reporting no significant difference in the outcomes across the two treatment conditions. The authors proposed the findings support the feasibility of developing a stepped-care treatment approach for providing care to clients with varying risk profiles.

Empirically evaluated interventions to date are typically considered lengthy, e.g. 12-month programmes and long waitlists for these therapeutic options have resulted in poor access to timely care. Despite this, there is little evidence supporting the intensity of treatment, measured in hours and duration; Storebø et al. [30] states: “We compared the effects of less than six months versus six to 12 months versus above 12 months duration for the outcome of BPD symptom severity. We found no evidence of significant differences between the subgroups” p. 65.

Further, DSM V criteria require that individuals satisfy only five of the nine diagnostic criteria to meet diagnosis; in effect, this results in 256 possible combinations or presentations of the disorder [19]. Given the subsequent heterogeneity of presentation, a “one-size-fits-all” treatment approach is arguably not sufficient for this population. A recent review of treatment for BPD found five psychotherapeutic interventions equally efficacious and with notable commonality in approach [15]. The authors proposed that the availability of more than one type of therapeutic intervention would better address issues with heterogeneity, patient preferences and finite resources. Further, Huxley et al. [10] reported on the effectiveness of a brief 3–4 session intervention as an initial step in the treatment journey. The authors noted that the variety of pathways patients followed subsequent to the intervention was reflective of the heterogeneity of crisis presentation, supporting the importance of variety in intensity and treatment type for this population. The need for further research investigating the effectiveness of modified structures in service provision, e.g. stepped care, and the identification of pre-treatment variables, e.g. diagnostic criteria to guide treatment choice and intensity, is clearly evident.

## Stepped care

Psychological therapy is considered as a primary intervention for people with BPD (National [23]); however, the finite resources of mental health services are challenged by client need and have historically fallen short in providing timely access to appropriate care. A recent review of care for people with BPD by Lawn and McMahon [13] noted that 52.5% of respondents (n = 105) reported difficulty in accessing care, attributing this to lengthy waitlists, financial barriers, physical distance to care and dismissing attitudes from health staff. Implementing stepped-care psychological therapy models compared to treatment as usual has been shown in a randomised controlled trial to reduce demand for hospital services, including re-presentations to hospital, shorter bed days and thus significantly reducing costs [8]. A follow-up study demonstrated how the stepped-care psychological approach retained people in care and reduced BPD symptoms and increased quality of life [10].

Stepped-care approaches, which are more responsive to client need, provide an alternative to fixed longer-term models that have high dropout rates [15]. The National Institute for Health and Clinical Excellence [25] guidelines support the adoption of stepped-care models to better meet the needs of clients with mental health problems. Stepped care is designed to more adequately address patient needs by improving accessibility to care and adjusting treatment intensity in health care settings with limited resources [25]. Stepped-care treatment is underpinned by two principles. Firstly, treatment provided is “least restrictive”, and secondly, it is “self-correcting”. In the context of public health services, these principles are applied by orientating stepped-care models towards providing treatment access to the minimal required specialist treatment (*least restrictive*), with the flexibility to step up or down (*self-correcting*) as warranted and based on individually tailored clinical decision-making, e.g. increase in acuity, poor response to care [3]. Stepped-care models are implemented as either progressive or stratified. A progressive model is one where the individual begins treatment with minimal intensity, e.g. brief or internet-based and progresses through a line of treatment options with increasing intensity in regard to clinician contact and format (group vs individual). A stratified model relies on individual assessment to gauge client need and enters them into the treatment phase most appropriate to clinical presentation [26]. To date, there has been limited research exploring the variables that may predict stepping up or down in care, despite its clear importance for ensuring the effective implementation of the stepped-care approach.

## Objectives

The proposed study aims to evaluate the effectiveness of a stepped-care structured psychological intervention for BPD when compared with treatment as usual. Specifically, the research seeks to answer: Is a stepped approach effective in treating BPD? This will be answered through the following questions.
(i)Is there a difference in outcomes for clients receiving group intervention or treatment as usual?

Hypothesis 1. Patients in the group treatment will demonstrate an equivalent reduction in BPD symptoms to participants in the treatment as usual (TAU) condition.
(ii)Do changes in symptoms and functioning during treatment persist following treatment?

Hypothesis 2. Participants in the group treatment will report an equivalent reduction in BPD symptom severity to participants in the TAU condition following treatment.
(iii)What implications does a stepped-care approach have for health services (including economic, treatment focus)?

Hypothesis 3. Participants in the group treatment will experience an equivalent reduction in length of admission and acute care following treatment compared to participants in the TAU condition.

This study is being conducted within two community mental health services which positions it as a pragmatic trial designed to provide valuable information regarding the real-world effectiveness of stepped-care treatment for BPD compared to existing care (treatment as usual).

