## Research design and methods

### Study design

The current study is a multi-centre, prospective, randomised, non-blind, superiority parallel arm trial comparing a stepped-care model of stand-alone DBT group skills therapy with treatment as usual. The subject of this evaluation is a two-step care model that was developed to address the finite resources within local community mental health services (see Fig. 1 for the trial design flow chart). Referrals for treatment will be made through a central mental health intake line or emergency department. All participants will complete a diagnostic assessment to determine suitability for the study. Following recruitment, participants will be randomly allocated to one of the two conditions. The treatment condition (group skills therapy) will be a manualised DBT programme.

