#### Primary analyses

The effect of treatment on primary outcomes will be evaluated using a linear mixed models approach, to account for the repeated measured structure of the data (SPSS-25). The data will be analysed as an intention-to-treat with time as a repeated measure. Recommended as the gold standard for study designs of this nature, this design (i) allows for the assessment of individual trends over time, with sensitivity to detect change; (ii) takes into account the longitudinal nature, utilising all data available; and (iii) controls for any pre-intervention differences [9, 27]. A linear mixed models analysis will be performed for each primary outcome variable symptom reduction (total number of BPD symptoms measured by the MSI-BPD) and service utilisation (inpatient hospital admissions and emergency department presentations). Change over time on these variables will be modelled as a within-subject effect of time, and the effectiveness of the intervention conditions will be determined by significant two-way group × time interaction. Although the change between baseline and end of the 16-week treatment block is of primary interest, three time points will be included to also examine the change during treatment and whether any changes are maintained following treatment. Within- and between-group effect sizes will be calculated, compared and interpreted according to the Cohen [5] recommendations.

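### All three hypotheses predict equivalence with treatment as usual, but the trial is declared, sized and decided as a test of difference with no margin, so its decision rule cannot confirm them

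*Protocol article*

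**What the plan says.** **Objectives.** Research question (i) asks about a difference: "Is there a difference in outcomes for clients receiving group intervention or treatment as usual". The hypothesis under it predicts the opposite kind of result: "Patients in the group treatment will demonstrate an equivalent reduction in BPD symptoms to participants in the treatment as usual (TAU) condition". Hypothesis 2 reads "Participants in the group treatment will report an equivalent reduction in BPD symptom severity to participants in the TAU condition following treatment". Hypothesis 3, on service use, reads "Participants in the group treatment will experience an equivalent reduction in length of admission and acute care following treatment" when set against treatment as usual (TAU).

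**Study design.** The trial is a "multi-centre, prospective, randomised, non-blind, superiority parallel arm trial".

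**Sample size and power analysis.** The trial is sized to detect a difference equal to 16% of a baseline MSI-BPD mean of 8.16, with SD 2.08, 80% power and alpha .05. This gives 40 per group, or 58 per group (N = 116) after 30% dropout. Service use is not sized.

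**Primary analyses.** For each primary outcome, "the effectiveness of the intervention conditions will be determined by significant two-way group × time interaction" in a linear mixed model.

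**Trial status.** 125 participants had been recruited when the article was written.

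**The concern.** Equivalence and superiority have different null hypotheses. A superiority test starts from no difference and looks for evidence against it. An equivalence test starts from a difference at least as large as a stated margin and looks for evidence that the true difference is smaller. The Objectives are written in the second framework, and the design label and decision rule in the first.

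At stake is how the primary result is read. A significant interaction is evidence that the arms differ, which is not what the hypotheses predict. A non-significant one shows only that no difference was detected, and that outcome becomes more likely as the data get fewer or noisier. Following the plan exactly therefore leads to no valid conclusion on any of its three hypotheses.

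**Working it through.** **1. What kind of calculation gives 40 per arm?** Inputs are from the Sample size and power analysis section.

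- Difference: 0.16 × 8.16 = 1.3056 points; SD 2.08.
- Two-sided 5%, 80% power: n = 2 × (1.960 + 0.842)² × 2.08² / 1.3056² = 39.8, so 40 per arm.
- Dropout: 40 / 0.70 = 57.1, so 58 per arm, N = 116.

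The plan's figures reproduce exactly as an ordinary two-sample test of a difference. One-sided 5% would give 32 per arm, and a paired one-sample calculation 20 in total, so neither is what was done.

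**2. Can the decision rule confirm the hypotheses?**

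- Significant interaction: the confidence interval for the difference excludes zero. The difference might still be small enough to count as equivalent, but without a margin nobody can say so. Equivalence is not confirmed.
- Non-significant interaction: the interval includes zero, but may also include differences that matter. Equivalence is not confirmed.

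**3. How uninformative is non-significance?** The planned test concerns change over time, so its SD depends on the correlation r between baseline and follow-up. The article does not give r, so I assume 0.3, 0.5 and 0.7, with equal SDs at both times and 40 completers per arm.

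- SD of change = 2.08 × √(2(1 − r)).
- SE of the between-arm difference = SD of change × √(2/40).
- The chance of non-significance uses a two-sample t-test, two-sided 5%, at a true difference of 1.0 point.
- Equivalence power uses two one-sided tests (TOST) at 5% each, true difference 0: 2Φ(margin/SE − 1.645) − 1. The margin of 1.31 is my assumption: the plan's whole 16% difference, 1.3056, used as a margin.

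| r | SD of change | SE | Non-significant at a true 1.0 | TOST power at margin 1.31 |
|---|---|---|---|---|
| 0.3 | 2.46 | 0.550 | 57% | 53% |
| 0.5 | 2.08 | 0.465 | 44% | 76% |
| 0.7 | 1.61 | 0.360 | 22% | 95% |

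Worked line for r = 0.5: SE = 2.08 × √(2/40) = 0.465; 1.3056/0.465 − 1.645 = 1.162; 2Φ(1.162) − 1 = 0.755.

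**4. What would equivalence need?** At r = 0.5, 80% power and a margin of 1.31: n = 2 × (2.08 × (1.645 + 1.282)/1.3056)² = 43.5, so 44 completers per arm (N = 126 after dropout). An assumed margin of 1.0 would need 75 per arm (N = 216).

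**The case against.** **A separate analysis plan or the full protocol may define a margin.** This is fair, and the absence of a margin from a condensed article is not the finding. But a margin stated elsewhere would not remove the conflict between the hypotheses and the declared superiority design with its significance rule.

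**The percentages do not describe the planned mixed model.** This stands in part. They use a baseline SD from another study in a simple two-arm comparison. At r = 0.5 the SD of change equals 2.08; at other correlations the figures move a good deal, which is why a range is shown. They cover the MSI-BPD only, and nothing is computed for Hypothesis 3. The defect is logical and does not depend on them.

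**The same 40 per arm would serve a non-inferiority design.** This is arithmetically true, with a margin of 1.3056 and one-sided 2.5%. The sample size section does not use the word superiority, and the article's emphasis on limited resources could motivate non-inferiority. But the 16% is never presented as a margin; it is described as a within-subject reduction. Nor is non-inferiority what the hypotheses state.

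**Two stronger readings are tempting and not supported.** A reader might infer that a significant interaction would contradict the hypotheses. It would not strictly do so, because a significant difference can lie inside an equivalence margin; it only fails to confirm them. A reader might also infer that the investigators intend to treat non-significance as proof of equivalence. The article does not say so, and it also promises between-group effect sizes. The wording leaves that reading open without committing to it.

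**Conclusion.** The contradiction is on the face of the article: three equivalence hypotheses against a superiority label, a difference-based sample size for the MSI-BPD, and a significance rule that contains no margin. It must be fixed, because the framework determines what the primary result means.

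The figures in the table are illustrations. They rest on SD 2.08 at both times, 40 completers per arm and the assumed correlations; the equivalence power also rests on an assumed margin. Within those limits, a non-significant result would be weak evidence of equivalence. At r = 0.5 or lower, the planned completers would give less than 80% power for equivalence even at the generous margin of 1.31; at r = 0.7 power would be ample at that margin.

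Timing matters. With 125 recruited against a target of 116, design-stage choices are largely past, and the framework has to be settled without sight of outcomes by arm.

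**What to change.** Before any outcome data are seen by arm, choose one framework and align Objectives, Study design, Sample size and power analysis, and Primary analyses with it.

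- **Default, matching the declared design and test:** reword Hypotheses 1 to 3 as superiority (or difference) hypotheses. State that a non-significant interaction will not be interpreted as equivalence. Report the between-arm difference with its 95% CI.
- **If equivalence or non-inferiority is really intended:** change the design label, prespecify a justified margin for each primary outcome, replace the significance rule by a rule on the confidence interval relative to that margin, and state the power that the achieved sample gives.

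Record the decision and its date in the registry.

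The default needs edits to three hypotheses, a sentence or two in the analysis plan and a registry update, with no new data. It is still a substantive change of stated hypothesis in a non-blind trial past its recruitment target, which is why the date and the absence of access to outcomes by arm should be documented. The downside is that equivalence can no longer be claimed from a non-significant test.

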**Fig. 1 Fig1:**
[figure not shown]
Proposed trial design evaluating stepped group skills training interventions. Note. *All participants will be contacted 16 weeks post-intervention, independent of the number of sessions completed. **Number of participants expected at each time point (inclusive of a dropout rate of 30%)

The group skills treatment will involve two steps. The treatment group will be offered a weekly, 2-h group treatment for 12 weeks. Following completion of the 12-week group, suitability for inclusion in the second step of group treatment (16-week skills group) will be assessed based on group attendance and clinical indicators: criteria for inclusion in continuing treatment includes meeting > 4 BPD diagnostic criteria or severity on GAF (< 65) at the completion of the 12-week group. Similarly, participants in the TAU condition will be retained in treatment through the additional 16-week period based on clinical need.

DBT targets the development of skills in mindfulness, emotional regulation, distress tolerance and interpersonal effectiveness [17]. Two separate group treatment manuals will be developed for the treatment condition. The manualised treatments will be based on the DBT skills and provide structured therapeutic intervention. The 12-week manual will provide an introduction to target skills and an opportunity to practise within the group. Participants will be encouraged to practise skills between sessions and provide feedback in the following session. The 16-week manual will expand on skills introduced in the 12-week manual. It will be delivered in a similar format, including in-session and between-session practice with a review.

Treatment as usual (TAU) refers to typical care provided by the trial sites. Participants randomised to this condition will be referred to the care pathways typically used by the public mental health site. These referrals will be informed by clinical decision-making and the presenting issues of the participant. As such, a range of treatment settings may be accessed in the TAU condition including case management within the local community mental health service, mental health rehabilitation services, referral to a local private psychologist or psychiatrist with known experience in working with BPD, local non-government organisations, general practitioners (GPs) and family and carer services. The TAU referral pathway will be specifically tailored to the participant presentation.

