### Baseline and follow-up evaluation

The McLean Screening Instrument for Borderline Personality Disorder ((MSI-BPD) [32] and the SCID-5-PD will be conducted at baseline for diagnosis. Evaluation will take place at the completion of the 12-week and 16-week interventions and 16 weeks following the end of treatment to assess the change in BPD symptom using the MSI-BPD. All participants will be contacted for assessment at these time points regardless of treatment arm or continuation in treatment.

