## Discussion

There has been a significant increase in knowledge regarding the effectiveness of psychological interventions in the treatment of BPD over the past 20 years, and it is now commonly held that structured psychological treatment is the primary treatment approach ([15, 23]). Despite this, health services are overwhelmed by the demand for services and struggle to provide timely access to treatment. The proposed stepped-care model provides a progressive treatment pathway for our evaluation. Findings from this study will help inform community mental health services in their mission to provide timely access to effective treatment with limited resources. Furthermore, data collected at baseline regarding symptomatology will assist our understanding of the impact of heterogeneity on treatment outcomes. It is hoped that this will help progress the development of diagnostic profiles for guiding treatment choice. The findings of this study will also provide important information about treatment dosage for BPD, and factors which may influence the need for greater or less intensive treatment.

There are several limitations in this study which relate primarily to it being conducted within two busy and active community mental health services that experience the problem of limited resources. Firstly, the inclusion of a treatment arm receiving the standard 12-month DBT treatment protocol could potentially provide greater confidence in significant treatment effects for the stepped-care model; however, this was not possible due to resource limitations. Secondly, we are unable to control the interventions provided to the TAU group. Consequently, the TAU group could potentially receive interventions that differ in intensity, therapeutic approach and mode of delivery, which therefore may affect the outcomes. Treatment as usual may also include referral to a number of services within the community. Although the follow-up survey will attempt to ascertain information regarding intensity and type of therapeutic approach, the accuracy of this information may vary.

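### Hypotheses 2 and 3 assume an end of treatment common to both arms, but the protocol fixes none for TAU, so week 52 cannot show persistence after treatment

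*Protocol article*

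**What the plan says.** The Objectives section poses question (ii), "Do changes in symptoms and functioning during treatment persist following treatment". Hypothesis 2 expects an "equivalent reduction in BPD symptom severity to participants in the TAU condition following treatment", and Hypothesis 3 an "equivalent reduction in length of admission and acute care following treatment compared to participants in the TAU condition". Primary analyses includes a time point after treatment to examine "whether any changes are maintained following treatment".

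Baseline and follow-up evaluation places the last symptom assessment "16 weeks following the end of treatment to assess the change in BPD symptom using the MSI-BPD". Service utilisation evaluation collects emergency and inpatient use in both arms over 16 weeks before recruitment and 16 weeks after treatment. Service use is one of the two primary outcomes (Primary outcomes).

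Table 1 puts randomisation at week 0, the first group step at weeks 4 to 16, the second at weeks 20 to 36, TAU at weeks 4 to 36, and follow-up at week 52.

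On the content of TAU, the Study design section (text after Fig. 1) says that "a range of treatment settings may be accessed in the TAU condition including case management within the local community mental health service", and adds rehabilitation, private, non-government, GP and carer services. On its duration it says only that "participants in the TAU condition will be retained in treatment through the additional 16-week period based on clinical need". The Discussion concedes that "we are unable to control the interventions provided to the TAU group" and names intensity, therapeutic approach and mode of delivery as what may differ. It does not name duration.

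**The concern.** A comparison after treatment needs an end of treatment in each arm. In the group arm this is a real event: the last session of the step the participant reached. In the TAU arm it is only a span in Table 1. The care itself consists of referrals to services that the trial does not run, and nothing in the text stops them at week 36.

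This affects what a week-52 result would mean. If the group arm loses ground relative to TAU between weeks 36 and 52, its benefit may have faded, or TAU participants may still be in care. If the arms look alike, a finished programme may be matching continuing care, which is a different and more favourable finding than equal persistence. Emergency and inpatient use has the same ambiguity. It matters more there, because the only post-baseline window stated for that primary outcome is the post-treatment one, and Economic analyses draws on the same presentations and admissions.

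**Working it through.** **1. The plan's own figure.** Inputs from Sample size and power analysis: baseline MSI-BPD mean 8.16, SD 2.08, reduction 16%, power 80%, alpha 0.05 (taken as two-sided), dropout 30%.

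- Difference: 0.16 × 8.16 = 1.3056 points.
- n per arm = 2 × (1.960 + 0.842)² × (2.08 / 1.3056)² = 39.8, rounded up to 40.
- After dropout: 40 / 0.70 = 57.1, rounded up to 58 per arm, 116 in total.

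The stated 40, 58 and 116 reproduce. The calculation refers to the end of the 16-week block, so it does not depend on the follow-up definition.

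**2. When 16 weeks after treatment falls.** End weeks are from Table 1.

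| Path | Treatment ends | 16 weeks later |
|---|---|---|
| Group, both steps | week 36 | 36 + 16 = week 52 |
| Group, first step only | week 16 | 16 + 16 = week 32 |
| TAU, by Table 1 | week 36 | 36 + 16 = week 52 |
| TAU, by Study design and Discussion | not stated | not defined |

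Table 1 has one follow-up column, week 52. Read literally, the service-use window of a participant who stops after the first step is weeks 16 to 32. For someone who completes both steps it is weeks 36 to 52. These windows do not overlap. If instead everyone is followed at week 52, the first participant is 52 − 16 = 36 weeks past the group and the second 52 − 36 = 16 weeks past it.

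**3. Whether TAU ends at week 36.** Table 1 gives an end week. Study design says that TAU is retained through the additional 16 weeks according to need, and lists providers whose care has no stated end date. The Discussion says that the trial does not control what they provide. No section says that care stops at week 36, or defines the end of TAU for an individual.

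**4. Whether the effect can be sized.** Let b be the benefit, in MSI-BPD points, of being in care at week 52, assumed equal for all. Let pT and pG be the shares of TAU and group participants then in care. The week-52 difference shifts by b × (pT − pG). The documents give none of these three quantities. They also do not say whether group participants receive other care, so even the sign of pT − pG is open. Any numerical shift would only restate the values chosen for it.

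**The case against.** The strongest reply is that this is a pragmatic trial analysed by intention to treat. Comparing the assigned arms at week 52 is then a valid comparison of two strategies, whatever care each arm goes on to receive. That stands, and the fix keeps it. What fails is the further step of calling the comparison persistence after treatment.

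Baseline and follow-up evaluation also says that everyone is contacted at the same points regardless of arm or continuation, and a note to Fig. 1 is similar. This suggests that a fixed schedule was meant. If so, the schedule is sound and the post-treatment label is what needs correcting.

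Several stronger readings are tempting, but the documents do not support them:

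- *TAU is open-ended.* This is an inference. Table 1 bounds TAU at week 36; the text simply does not show that care stops there.
- *Group participants are untreated at week 52.* No section says so or bars them from other care. If both arms receive usual community care after week 36, the asymmetry shrinks or disappears.
- *The gap in weeks 16 to 36 is a flaw.* Finishing after the first step when the step-up criteria are not met is part of the stepped-care strategy under test.
- *The trial cannot tell what care was received.* The Discussion plans a follow-up survey of intensity and type of therapy, though it expects varying accuracy. Table 1 shows no item on care received at week 52, but an article need not itemise its questionnaires.

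The Discussion's admission about uncontrolled TAU does not settle the matter, since it does not mention duration.

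**Conclusion.** The point holds in limited form. Hypotheses 2 and 3, the maintenance aim in Primary analyses and the post-treatment windows for symptoms and service use rest on a common end of treatment that the protocol does not establish. For TAU it is only a table entry. In the group arm it is week 16 or week 36, depending on stepping up. Week 52 may therefore compare a completed programme with continuing TAU, and the between-arm contrast cannot support a claim that benefit persists after treatment.

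The baseline to end-of-16-week-block symptom contrast, which the plan calls its main interest, is untouched, as is the sample size. The magnitude is unknown and cannot be derived from the documents. The conclusion does not assume that TAU actually continues past week 36, only that the protocol neither excludes this nor defines the alternative. It deserves correction because it changes what Hypotheses 2 and 3 can conclude, including for a primary outcome.

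**What to change.** 1. Define the follow-up assessment and the service-use window for both arms in weeks since randomisation, for example week 52 and weeks 36 to 52 (52 − 36 = 16 weeks, the length already planned). Reconcile Table 1's TAU span with Study design, Baseline and follow-up evaluation, Service utilisation evaluation and the Discussion. This concerns measurement windows only; how long care should last is not a matter for this review.
2. Word Hypotheses 2 and 3 and the maintenance sentence in Primary analyses as an intention-to-treat comparison of the two strategies at week 52. Draw no claim of persistence after treatment from the between-arm contrast. Label any change within the group arm after week 36 as descriptive and uncontrolled.
3. Use the follow-up survey already planned to ask both arms the same short items at the remaining scheduled contacts: whether in treatment now, provider type, and any DBT or BPD-specific therapy. Report the answers by arm beside the week-36 and week-52 results.

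The cost is a narrower maintenance claim and a few extra items. Care data will be incomplete for participants already past those contacts: Trial status reports 125 recruited, with recruitment open since October 2018. Steps 1 and 2 can still be applied to everyone.
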